## Abstract

**Background:**

Mpox disease is endemic to several regions of sub-Saharan Africa, with transmission occurring through close contact with infected animals or humans. Increasing case numbers in East Africa led the African Centre for Disease Control and Prevention to declare a Public Health Emergency of Continental Security on 13th August 2024 related to a new virus variant (clade 1b). The Mpox CARE study aims to establish clinical and epidemiology data to develop innovative immunodiagnostic tests, facilitating models for sub-clinical disease exposure, transmission and future vaccine strategies (Part A). Furthermore, we aim to evaluate and optimize vaccine cold-chain (VCC) systems to support Mpox vaccine deployment while ensuring the continued provision of childhood immunizations (Part B).

**Methods:**

This study will recruit up to 650 participants to three study groups according to Mpox exposure status and/or vaccination in Rwanda. All enrolled participants will be asked to provide demographic information, relevant medical history, up to 20mLs of venous blood and a dried blood spot capillary blood sample. For Part A of the study, samples will undergo testing for quantitative analysis of total serum antibody to Mpox specific proteins using an enzyme-linked immunosorbent assay (ELISA) and test a novel point-of-care (POC) lateral flow test to determine positive/negative qualitative serostatus. For Part B, we will collect data on VCC equipment, inventories and methods of vaccine distribution. The results of this project aim to (a) validate a blood-based ELISA assay for the detection of Mpox immunity in a target population of Rwanda, (b) generate an estimate of sero-positivity to Mpox in Rwanda, (c) evaluate the clinical performance of a novel POC lateral flow test for Mpox serostatus and (d) understand the VCC requirements for additional vaccine deployment for disease control.

**Discussion:**

Detecting antibodies for sub-clinical Mpox cases improves disease mapping and transmission patterns in endemic African regions. Novel POC immunodiagnostics can enhance community healthcare and decentralise efforts to understand Mpox seroepidemiology. Understanding VCC requirements for deployment of genetic vaccines, alongside regular vaccine provision to pregnant women, and children offers insights for management of future vaccine-preventable disease outbreaks.

**Trail registration:**

Clinicaltrials.gov trial registration number NCT06887556, registered 20th March 2025.

## Background

Mpox disease is caused by human Monkeypox virus (hMPXV), a member of the *Orthopoxvirus* (OPXV) genus [1]. Transmission occurs through close contact with infected animals’ mucosa, for example via animal bites or consumption of improperly cooked infected animals [2, 3], and between humans either through the respiratory tract or skin-to-skin contact, for example during sexual intercourse [2, 4]. Clinical infection includes coryza, fever, lymphadenopathy and the characteristic vesicular centrifugal rash [2]. Morbidity and mortality are usually secondary to bronchopneumonia, bacterial superinfection, encephalitis, keratitis leading to visual loss, or dehydration through gastrointestinal loss [3, 5]. Mpox is predominantly endemic to central and West Africa, but sporadic cases occur throughout the world [5].

Whole genome sequencing has identified two distinct clades of virus with different clinical and epidemiological features [6]. Clade I is endemic to Central Africa and the Congo Basin and is more virulent [7] than Clade II with a case fatality rate (CFR) of 10.6% [8]. Clade II is endemic to West Africa and has a CFR of approximately 4% [8]. A subset of this clade, subclade IIb lineage B.1 was responsible for the 2022 outbreak [9] when, in July 2022, the World Health Organization (WHO) declared a public health emergency of international concern (PHEIC, to May 2023) under the International Health Regulations (2005) following outbreaks in all six WHO regions [10, 11]. In 2024 case numbers in the Democratic Republic of Congo (DRC) began steadily rising [12], eventually spreading into neighbouring countries triggering the African Centre for Disease Control and Prevention to declare a Public Health Emergency of Continental Security on 13th August 2024 [13]. There are two strains of circulating virus, clade Ia (previously known as clade I) in northwestern DRC primarily affecting children, and a new strain clade Ib in northeastern DRC which has since spread to bordering countries [14]. The clade Ib strain (sub-lineage A) was first identified in South Kivu [15] and has been found to have a APOBEC3-type mutations thought to confer increased transmission between humans. Between 1 January 2024 and 2 February 2025 there have been 21,113 confirmed Mpox cases with 70 deaths [16]. The WHO released 1.45 million USD in August 2024 to fund needs-based access to smallpox vaccines in the region; however, there is currently limited global availability [17].

The clade 1b Mpox outbreak is an urgent public health emergency in need of additional scientific countermeasures to control the spread of disease and protect African communities. There are currently three vaccines recommended for use by the WHO for prevention of Mpox; (1) ACAM2000, a replication competent vaccinia virus and a second-generation smallpox vaccine (2), MVA-BN, a non-replicating modified vaccinia virus Ankara vaccine, and (3) LC16, a live attenuated minimally replicating vaccinia virus vaccine [18]. Vaccination is recommended for those at high risk of exposure, or as post-exposure prophylaxis within two weeks of significant exposure to Mpox [18]. There are no known immune correlates of protection; however, antibody titres are thought to be a potential surrogate for protection based on challenge studies with B cell depleted macaques [19]. Duration of vaccine protection is unknown. In longitudinal studies following smallpox vaccination, anti-vaccinia antibody titres measured by ELISA, as well as serum neutralising antibody titres are maintained above the presumed protective threshold for 75 years [20], and T-cell immunity also appears to be maintained for at least 20 years [20]. Data on how this translates to protection from Mpox remains limited. Development of Mpox specific immunological assays using OPXV-specific antibody profiles [21, 22]can help to distinguish between vaccine immunity, natural/hybrid immunity and cross reactive antibody from related poxvirus exposure, and improve our understanding of disease transmission and priorities for vaccination. The purpose of this study is to establish two immunodiagnostic assays to detect mpox-specific antibody in the Rwandan population; an ELISA and a blood-based lateral flow test. This study will also measure the capacity of Rwanda’s vaccine cold chain network to determine it is able to accommodate rapid mpox vaccine deployment for outbreak control purposes without disruption to routine childhood vaccination.

## Methods and analysis

### Study design and setting

This study consists of two parts (Fig. 1).

**Fig. 1 Fig1:**
[figure not shown]
Schematic presentation of the protocol

Part A will run in two stages, the first will validate an mpox-specific ELISA developed at University of Birmingham in a Rwandan laboratory with Rwandan samples of known clinical or vaccinated mpox status. The second stage will use this ELISA once successfully validated to perform a seroepidemiology study and evaluate the performance of a lateral flow test to identify the presence of mpox-specific antibody.

For Part B we aim to understand the vaccine cold-chain (VCC) operational needs for real-world impact of Mpox vaccines deployed for disease control.

Following rapid implementation of outbreak control measures including being the first in the region to administer mpox vaccines via a ring vaccination strategy [23], case numbers in Rwanda have remained low reaching 127 as of 5th October 2025, compared to 34,000 cases in the Democratic Republic of Congo [24]. Rwanda was selected as the study setting due to its epidemiological relevance and robust public health infrastructure. Rwanda neighbours both Uganda and DRC and we expect some overlap in background infections with cross reactivity with the ELISA, and we believe this will provide data applicable to the wider region.

The availability of meticulous vaccination and infection records enables the robust selection of well-defined mpox-case, MVA-BN vaccinated, and mpox-unexposed control groups. This structured approach, paired with the representative nature of the Rwandan Vaccine Cold Chain (managed by the Rwanda Biomedical Centre, RBC), ensures the study findings are highly applicable and generalizable to other African nations facing significant Mpox outbreaks.

## Aims and objectives

### Primary aims and objectives

Part A: The **primary clinical aim** of this study to validate novel immunodiagnostic tools to estimate Mpox sero-prevalence. Primary clinical objectives include:

The collection of biological samples (blood) and clinical metadata from human volunteers at risk of Mpox or who have had past Mpox infection/vaccination.To verify a serum-based ELISA quantitative screening assay, for the detection of anti-Mpox specific IgG antibody, in a Rwandan population with equivalent sensitivity for clade 1a Mpox compared with the clade IIb that it was established for.To validate a prototype blood-based, binary or categorical (sero-positive/sero-negative) point-of-care lateral flow test (POC LFT) for the detection of anti-Mpox specific IgG antibody to inform further development and optimisation.

Part B: The **primary public health aim** is to understand the vaccine cold-chain readiness to deploy Mpox vaccines without detrimental effects on existing WHO EPI and other vaccine supply.

Primary public health objectives include:

To measure the available capacity within sub-networks of the vaccine cold-chain in Rwanda to deploy Mpox vaccines into target populations.To model different modes of vaccine deployment scenarios for most efficient vaccine use and public health impact.

The primary endpoints of this study are

anti-Mpox specific IgG titres as measured by the ELISA,Binary lateral flow test result.Capacity of the VCC in Rwanda as measured by number of vaccine vials stored at max capacity.

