### Sample size

#### Part A

The first stage of part A will involve validation of the University of Birmingham-developed multiplex ELISA evaluated on UK samples by University of Birmingham and UKHSA following Mpox infection with clade II virus and/or vaccination [25], using *N* = 50 samples each from groups 2b, 2d and group 3. The ELISA uses several Mpox proteins and shows excellent concordance with a multiplex bead assay developed by the UKHSA [25] on UK samples, with high sensitivity/specificity for identifying seropositivity. The performance of the ELISA will be evaluated on Rwandan participants with known status to evaluate the effect of factors such as ethnicity, nutritional status, chronic viral infection (e.g. HIV or hepatitis B) and pathogen factors such as clade Ib virus (the cause of the current outbreak) on test performance. The sub-group specific recruitment targets have therefore been expanded by 50% to accommodate potential confounders and improve the stability of estimates applied to this component of the study and the next steps in validation and assessment of clinical accuracy of novel POC LFTs. Once the performance of the Mpox ELISA is confirmed in serum, alternative sample matrices including plasma and dried blood spot (DBS) will be compared to IgG titres measured in serum in paired samples.

There is a lack of data on the current sero-prevalence of Mpox-specific immunity, which this study aims to address, meaning statistically driven power calculations are challenging. Sample sizes have been calculated according to Clinical & Laboratory Standards Institute standards and consistency with the design, setup and verification protocols used for new infectious diseases targets.

The sample size calculation has been derived from the assumption of 20% seroprevalence in the intended target-use population (high-risk individuals with no known past infection/vaccination), plus added assumptions of a 5% margin of error and a 10% allowance for the withdrawal of consent from any participants, missing data, and assay failures/invalid test results.

In total, *N* = 500 is required for this part of the study from the following study groups:

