### Statistical analysis plan

#### Part A

The analyses for this study will be primarily descriptive in purpose (counts/proportions, or geometric mean titre where appropriate) and will not include any hypothesis testing. Comparative analyses (chi-squared/Fisher-exact or paired/unpaired t-test where appropriate) and the presentation of p values will represent post-hoc analyses.

ELISA performance will be assessed by a receiver operating characteristic (ROC) curve and area under the curve analysed to evaluate the ability of the ELISA to distinguish those presumed seropositive (vaccination and infection) from seronegative (no known infection or vaccination). The best cut-off for identifying serostatus will be selected using this method based off the highest sensitivity and specificity.

The Mpox POC LFT performance will be evaluated versus the ELISA and characterised by positive/negative concordance, correlation, test sensitivity, specificity, positive predictive value (PPV), negative predictive value (NPV) and likelihood ratios. The views and perspectives gained from the semi structured interviews will be analysed qualitatively on a small subset of participants (*n* = 30).

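### The primary ELISA objective claims equivalent sensitivity for clade 1a, but the outbreak clade is 1b and the stated analysis gives no infection-specific sensitivity to compare with clade IIb

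*Protocol article*

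**What the plan says.** All places are in the protocol article.

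- **Primary aims and objectives, Part A.** The ELISA is to be verified in a Rwandan population "with equivalent sensitivity for clade 1a Mpox compared with the clade IIb that it was established for".
- **Abstract and Background.** The abstract attributes the 2024 emergency to clade 1b. The Background says "The clade 1b Mpox outbreak is an urgent public health emergency". It describes "clade Ia (previously known as clade I) in northwestern DRC primarily affecting children" and, by contrast, "a new strain clade Ib in northeastern DRC which has since spread to bordering countries".
- **Sample size, Part A.** Stage 1 uses 50 samples from each of Groups 2b (infected over a month ago), 2d (vaccinated over a month ago) and 3 (controls). Among the influences to be examined are "pathogen factors such as clade Ib virus (the cause of the current outbreak) on test performance". The earlier evaluation was on UK samples after clade II infection and/or vaccination. It is described only as showing high sensitivity and specificity, with no values or counts.
- **Statistical analysis plan, Part A.** The analyses are mainly descriptive "and will not include any hypothesis testing", and "the presentation of p values will represent post-hoc analyses". ELISA performance is assessed by one ROC curve, with infected and vaccinated participants together as presumed positives and Group 3 as negatives. The best cut-off is chosen from that same curve.

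**The concern.** Two parts of the plan do not fit the objective. First, the clade named in it differs from the clade that the rest of the article treats as the target. Second, equivalent sensitivity is a comparative claim about infected people, while the only ELISA analysis described neither isolates infected people nor compares them with the clade IIb data.

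The stakes go beyond wording. Under Study design and setting, the ELISA moves to the seroepidemiology stage once it has been successfully validated. Under Laboratory analysis, it then becomes the reference standard for the lateral flow test. If the objective names one clade and the analysis cannot speak to the comparison, it is unclear what successful validation means.

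**Working it through.** **1. Clade, set side by side.** The objective says 1a. The abstract, the Background and the sample-size section say 1b/Ib for the current outbreak. The Background puts Ia in northwestern DRC and says Ib reached bordering countries; Study design and setting notes that Rwanda neighbours DRC. No study group is defined by clade. Group 2 accepts clinically confirmed cases (Table 1) and generic orthopoxvirus PCR (Table 2), so eligibility does not establish clade. The natural expectation is that infected participants inform Ib, but this is an inference: no text states the clade of the Rwandan cases.

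**2. What the ROC analysis yields.** Stage 1 positives are 50 infected (2b) plus 50 vaccinated (2d). As an illustration, suppose 90 of these 100 are detected, a pooled sensitivity of 90%. The 10 misses could all be infected or all be vaccinated:

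- all infected: 40/50 = 80% sensitivity after infection;
- all vaccinated: 50/50 = 100%.

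The pooled figure therefore does not fix the quantity in the objective. In addition, a cut-off chosen on the Rwandan data need not be the one behind the UK results, so even a split figure would differ from the UK estimate partly through the threshold.

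**3. The plan's own sample-size figures.** None is given for this objective. The stated inputs (20% seroprevalence, 5% margin of error, 10% allowance) concern prevalence: 1.96² × 0.20 × 0.80 / 0.05² = 246, and 246/0.90 ≈ 274. That does not reproduce the 330 in Group 1, but it is a separate matter. No input concerns sensitivity by clade.

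**4. Precision from 50 infected.** Normal half-width at 90%: 1.96 × √(0.9 × 0.1/50) = 0.083. Exact (Clopper-Pearson) 95% CIs:

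- 45/50: 78.2 to 96.7%
- 48/50: 86.3 to 99.5%
- 50/50: 92.9 to 100%

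With Group 2a added (n = 60), the half-width at 90% is 1.96 × √(0.09/60) = 0.076.

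**5. Equivalence power, over assumed values.** The article gives no margin or reference sensitivity, so both are assumed. Two one-sided tests at 0.05 each, no true difference: power = 2Φ(m/SE − 1.645) − 1, floored at 0. For a fixed benchmark SE = √(p(1−p)/50); for 50 against 50, SE = √(2p(1−p)/50).

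| Sensitivity p | Fixed: 5 pts | Fixed: 10 pts | Fixed: 15 pts | 50 v 50: 5 pts | 50 v 50: 10 pts | 50 v 50: 15 pts |
|---|---|---|---|---|---|---|
| 0.85 | 0.00 | 0.26 | 0.82 | 0.00 | 0.00 | 0.35 |
| 0.90 | 0.00 | 0.52 | 0.94 | 0.00 | 0.02 | 0.61 |
| 0.95 | 0.00 | 0.89 | 1.00 | 0.00 | 0.48 | 0.93 |
| 0.98 | 0.62 | 1.00 | 1.00 | 0.11 | 0.95 | 1.00 |

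Example: p = 0.90, fixed, 10 points: SE = 0.0424, 0.10/0.0424 − 1.645 = 0.71, power = 0.52. The answer runs from hopeless to ample across plausible inputs.

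**The case against.** The best defence is that 1a is a slip in a single line. The sample-size section states the intent with clade Ib, and an openly descriptive study may use *equivalent* loosely. That is plausible and makes the clade error cheap to correct. It does not rescue the comparison, because the described analysis still has no infection-specific sensitivity on a common cut-off.

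Four stronger readings are tempting and are not supported:

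- **That 50 cases are too few, so the objective cannot be met.** The table shows this depends on assumptions. Group 2a adds 10 infected who must also be fully recovered. If the ceiling of 650 means that stage 1 is additional to the 500 (500 + 3 × 50 = 650), up to 110 infected could be available.
- **That the sample contains no clade Ia.** The clade of the Rwandan cases is inferred, not stated.
- **That a missing margin is itself a fault.** A margin and details of the comparator could sit in the full protocol or SAP, which are not shown.
- **That a non-significant result would be declared a success.** No decision rule of that kind appears. Comparative p values are labelled post hoc and are not tied to this objective.

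**Conclusion.** The point holds on the text in two respects. The clade in a primary objective conflicts with the clade named throughout the rest of the article. The analysis as described cannot deliver the claim, because it excludes testing, pools infection with vaccination and re-selects the cut-off locally. The second problem survives correction of the first.

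The limited precision (about 78 to 97% for 45/50) is supporting evidence, not proof that equivalence is out of reach. The power range rests on assumed sensitivities of 85 to 98%, margins of 5 to 15 points, and either an error-free benchmark or a comparator of 50. Because this is a primary objective and validation of the ELISA opens the next stage, it should be corrected before results are interpreted.

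**What to change.** 1. Reconcile the clade in the primary objective with the abstract, the Background and the sample-size section.
2. Replace the equivalence wording with estimation: ELISA sensitivity in previously infected participants (Group 2b) with a 95% CI, and its difference from the UK clade IIb estimate with a 95% CI that carries the sampling error of both.
3. Report this at the cut-off already used for the UK data, separately from vaccinated participants, and show the result at the Rwandan ROC cut-off beside it. This assumes that the UK cut-off and the counts in infected people are available to the team.

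No change to groups, samples or data collection is needed. Enlarging the infected group is hardly an alternative: the article reports 127 Rwandan cases to 5 October 2025, of which 50 is already 39% and 60 is 47%. The cost is a more modest stated objective and one additional descriptive analysis.

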## Discussion

The recent 2024 outbreak occurred just 24 months after the previous outbreak and Mpox will remain an ongoing threat to the health security of low-middle income countries (LMICs). Development of both quantitative laboratory and qualitative point of care immune diagnostics, and implementation of robust vaccination programs where efficacious vaccines exist, are key components of outbreak management.

This study aims to establish Mpox serological testing capability in Rwanda and determine the capacity of the VCC to accommodate additional vaccine deployment. An ELISA is a simple method that is already used in most laboratories and POC LFTs can be used in the field, allowing both to be rolled out to other at-risk countries in the region to support strategies to control and prevent Mpox outbreaks.

As there is no established immune (antibody) correlate of protection, this diagnostic test will be unable to determine if individuals have protective immunity and therefore do not require vaccination. The assay will only measure total antibody to four mpox proteins, rather than functional antibody or T-cell response, which may not provide a full picture of immunity. In addition, there is significant homology between orthopox viruses, leading to cross-reactivity in the immune response. Another limitation of the study is that it will only be conducted in Rwanda, limiting the generalisability to other African nations. Part B of the study relies on manual data entry by staff at different parts of the VCC into a specialised app. To minimise the risk of errors, this app has been adapted from one previously used by staff for an earlier study, and they will be extensively trained.

This study is highly important due to its dual focus on precision diagnostics from a relevant (African) population and operational relevance to the use of vaccines for outbreak control. This study will help to address global health by providing diagnostic tools fit for use and accurate in mpox transmission regions. Simultaneously, quantifying the Rwandan vaccine cold-chain capacity is essential for planning the effective rollout of vaccines while safeguarding existing routine maternal and child health immunisation programs.

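### The only stated ELISA analysis pools infection with vaccination and does not use the four-protein profile, so it gives no sensitivity for infection alone and a Group 1 positive cannot be read as mpox infection

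*Protocol article*

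**What the plan says.** All references are to the protocol article.

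- **Statistical analysis plan, Part A.** The ROC curve is to "distinguish those presumed seropositive (vaccination and infection) from seronegative (no known infection or vaccination". On the threshold: "The best cut-off for identifying serostatus will be selected using this method based off the highest sensitivity and specificity". No other analysis of ELISA performance is stated.
- **Sample size, Part A.** Stage 1 validation uses 50 samples each from groups 2b (infected more than a month ago), 2d (vaccinated more than a month ago) and 3 (control). On the assay: "The ELISA uses several Mpox proteins".
- **Discussion.** "The assay will only measure total antibody to four mpox proteins". Orthopoxvirus cross-reactivity is named as a limitation.
- **Background.** Assays built on antibody profiles "can help to distinguish between vaccine immunity, natural/hybrid immunity and cross reactive antibody from related poxvirus exposure".
- **Primary aims and objectives.** The ELISA is to be verified as having equivalent sensitivity for one mpox clade compared with the clade IIb for which it was established. The endpoint is "anti-Mpox specific IgG titres as measured by the ELISA".
- **Study design and setting.** Ring vaccination has been used in Rwanda, and some cross-reactivity with the ELISA is expected.
- **Exclusion criteria (part A).** Known mpox infection excludes a person from Group 1. Earlier vaccination is not listed.
- **Abstract, Discussion.** Antibody detection is meant to improve mapping of sub-clinical cases.

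**The concern.** Three things depend on the ROC step: the cut-off, the serostatus call in the Group 1 seroepidemiology, and the reference standard for the lateral flow test. Pooling infection with vaccination at that step has two consequences.

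First, the sensitivity it yields is an average over two kinds of positive, half infected and half vaccinated in stage 1. The clade objective is about detecting infection, and the average can hide a deficit there.

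Second, a rule trained to separate any exposure from none says nothing about which exposure produced a positive. Group 1 includes close contacts of confirmed cases in a country that used ring vaccination, and ages run to 80, so past smallpox vaccination is also possible. If Group 1 positives are read as sub-clinical infection, the map of disease could largely be a map of vaccination and cross-reaction.

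A smaller issue is that cut-off and performance come from the same curve on the same samples, which makes the performance look better than it is.

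**Working it through.** The documents give no titre distributions, no sensitivity for Rwandan samples and no cross-reactivity rate. Steps 2 to 4 are therefore illustrations under assumed values; none is an estimate for this study.

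**1. What pooled sensitivity hides.** With 50 from 2b and 50 from 2d, pooled sensitivity = (x_2b + x_2d)/100. Suppose the result is 95/100 = 95% (exact 95% interval 88.7% to 98.4%). This is compatible with:
- 2b 45/50 = 90% (78.2% to 96.7%) and 2d 50/50 = 100% (92.9% to 100%);
- the same two results with the groups exchanged.

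The pooled figure cannot tell these apart. In the first case the lower limit for infection is about 10 points below the pooled lower limit (88.7 − 78.2 = 10.5).

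**2. What a Group 1 positive means.** Let i be the infected fraction, v the vaccinated fraction and f the positive rate among the rest through cross-reaction. Assume sensitivity 95% for both infection and vaccination.

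Crude positive rate = 0.95i + 0.95v + (1 − i − v)f. Infected share of positives = 0.95i / crude rate. Evaluable Group 1 = 330 × 0.90 = 297.

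| i | v | f | crude rate | positives of 297 | infected share |
|---|---|---|---|---|---|
| 10% | 0% | 2% | 0.095 + 0 + 0.018 = 11.3% | 34 | 84% |
| 10% | 10% | 5% | 0.095 + 0.095 + 0.040 = 23.0% | 68 | 41% |
| 5% | 10% | 10% | 0.0475 + 0.095 + 0.085 = 22.8% | 68 | 21% |
| 2% | 10% | 10% | 0.019 + 0.095 + 0.088 = 20.2% | 60 | 9% |

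The last three rows lie near the 20% seroprevalence assumed in the sample size section, yet the infected share differs more than fourfold.

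**3. What the profile could add.** Assume four log titres with unit variance and pairwise correlation 0.5, all raised by 3 SD after infection, and one protein lower by d SD after vaccination.

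- Summed titre, 2b v 2d: variance 4 + 12 × 0.5 = 10 per group, so AUC = Φ(d/√20).
- Linear discriminant on four titres: the squared distance is 1.6d² (1.6 is the diagonal of the inverse correlation matrix), so AUC = Φ(d√1.6/√2).

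| d | summed titre | four-protein profile |
|---|---|---|
| 0 | 0.50 | 0.50 |
| 0.5 | 0.54 | 0.67 |
| 1 | 0.59 | 0.81 |
| 2 | 0.67 | 0.96 |

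In simulations of the same four settings, the summed titre separates positive from control with AUC of 0.99 or more throughout. A rule can therefore pass the stated ROC analysis and still be near chance at separating infection from vaccine. At d = 0 the profile adds nothing.

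**4. Optimism of the selected cut-off.** I simulated 1,500 replicates with 100 positives and 50 controls, a shift of 2.56 SD and correlation 0.5. Choosing the cut-off by highest sensitivity plus specificity on one pre-fixed protein gives an apparent Youden index of 0.83 against a true 0.79. Choosing the best of four proteins as well gives an apparent 0.87, still against a true 0.79.

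**The case against.** The strongest reply is that the two-class ROC matches the stated aim. The Background gives the purpose as detecting mpox-specific antibody and says only that profiles can help with origin. No objective or endpoint promises to assign origin, and the Discussion admits cross-reactivity. This stands in part: the plan does not contradict itself, and a profile analysis is an addition. It does not answer the sensitivity-for-infection objective, nor the use of positives to map sub-clinical cases.

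A second reply is that the sample size section describes the target population as people without known earlier infection or vaccination, and that vaccination records are said to be meticulous. That helps only if the records are used. The Group 1 exclusions do not list vaccination, and records do not address cross-reactivity.

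A reader might infer three stronger points that the documents do not support:

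- *The endpoint reduces the assay to one titre.* The text says titres, in the plural, and does not state how the proteins are combined. That rule may sit in the full protocol, the SAP or the established assay procedure.
- *The profile information is discarded.* Quantitative titres are a primary endpoint, groups 2b, 2d and 3 are sampled separately, and exploratory immunology is a secondary objective. The profile is only absent from the stated analyses.
- *A three-class model on 2b, 2d and 3 would identify cross-reactive antibody.* No group is a cross-reactive reference. Take the step 4 shift and correlation, two proteins lower by 1 SD after vaccination and a uniform cross-reactive shift of 2 SD (all assumed). Such a model then calls about 60% of cross-reactive sera infected and 25% vaccinated.

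**Conclusion.** The point holds in a limited form. The one stated ELISA analysis pools infection with vaccination, selects a cut-off and reads performance from the same samples, and uses no antibody profile. It therefore yields no sensitivity for infection alone, and it supports reading a Group 1 positive only as orthopoxvirus seropositivity of any origin.

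These conclusions rest on the text: the ROC classes, the Group 1 exclusions and the expected cross-reactivity. The sizes do not. The 9% to 41% infected share, the AUC gains and the optimism of 0.04 (one fixed protein) to 0.08 (best of four) on the Youden scale all follow from assumed sensitivities, shifts and correlations. They show that the effect can be large, not how large it will be. Whether the profile helps depends on whether any of the four proteins differs between infection and vaccination, which the stage 1 samples can show. The matter deserves correction before analysis but does not invalidate the design.

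**What to change.** Change the analysis text in the Statistical analysis plan, Part A. No new samples are needed.

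1. Report the ROC curve, sensitivity and specificity separately for 2b v 3 and 2d v 3, with confidence intervals and a cross-validated (optimism-corrected) estimate at the selected cut-off. Use the 2b v 3 result for the clade objective.
2. Add a cross-validated 2b v 2d analysis of the four log titres. Only if it discriminates, report Group 1 positives as infection-like, vaccine-like or undetermined, with the threshold for undetermined set beforehand. State that no reference group exists for cross-reactive antibody, so infection-like does not exclude it.
3. Report Group 1 seropositivity by recorded vaccination history. Otherwise label it as orthopoxvirus seropositivity of any origin, wherever it feeds case mapping or vaccine targeting.

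The cost is analysis time and retrieval of vaccination history for Group 1. With 50 per group the profile estimates will be imprecise, some positives will stay undetermined, and step 2 may show that the profile adds nothing. That result would itself justify the any-origin label.
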